## Abstract

Since the 2022–2023 season in Portugal, a high-dose quadrivalent influenza vaccine is freely available for individuals living in long-term care facilities (LTCF). In 2024–2025, vaccination was extended to community-dwelling individuals aged ≥85 years. Given the scarcity of reported high-dose influenza vaccine effectiveness (IVE) estimates for this population, this study aims to estimate the high-dose relative and absolute IVE. A retrospective cohort study using data from electronic health records databases (EHR) will be implemented, using two cohorts, one of individuals vaccinated with influenza vaccine (to estimate relative IVE) and another of individuals eligible for the high-dose quadrivalent influenza vaccine (to estimate absolute IVE). We will consider two subgroups for both cohorts: individuals living in LTCF and community-dwelling individuals aged ≥85. We will use a fixed cohort approach, defining the eligible population by age at the vaccination campaign(s) start and living status. The outcomes are based on the primary cause of hospital admission. The reference population database will be defined by linking EHR on vaccination, comorbidities, and hospitalisations using a unique identifier through a deterministic data linkage procedure, and influenza vaccination status will be assessed retrospectively. We will use Cox proportional hazards regression models to estimate the hazard ratio (HR), considering as event the first hospitalisation due to influenza-like-illness and as exposure the vaccination status. IVE will be estimated as one minus the confounder-adjusted HR of vaccinated with the high-dose quadrivalent influenza vaccine vs vaccinated with standard dose (to estimate relative IVE) or unvaccinated (to estimate absolute IVE). While challenges such as EHR constraints and potential reporting bias pose limitations, using routinely collected data has successfully estimated COVID-19 VE and enables precise monitoring of VE with higher representativeness. The results of this study will inform the Health Ministry on the future influenza vaccine programme in Portugal.

## Background

In Portugal, as in most European countries, influenza seasonal immunisation is recommended annually to high risk individuals, which include, among others, elderly individuals (age stratification varies across seasons, i.e., aged ≥60 or aged ≥65 years) and those who reside in long-term care facilities (LTCF) [1].

Adults aged 65 or more are more prone to lower respiratory tract infections, including pneumonia, bronchitis, and tracheobronchitis, due to specific factors, such as genetic polymorphisms, chronic immunocompromised conditions, age and correspondent age-related comorbidities, that may compromise the individual capacity to produce an adequate immune response [2,3]. These infections are associated with considerable morbidity and can lead to hospitalisation, especially in frail older adults, such as those residing in LTCF [4]. There is a potentially different risk of exposure in older community-dwelling individuals due to the greater number of contacts. Additionally, LTCFs significantly contribute to the variability in exposure to the disease between individuals, resulting in greater individual susceptibility to severe outcomes [4,5].

Vaccination is widely considered the most effective intervention against influenza and its associated complications [5]. However, influenza vaccination strategies might target individuals who, although at high risk of influenza complications, may have impaired capacity for developing effective vaccine-induced immunity. Given the specificities of individuals in LTCF, the effect of influenza vaccination in this population needs further investigation [2,5]. A high-dose quadrivalent influenza vaccine was developed to provide greater protection and better prevent influenza-related complications than the standard dose influenza vaccine.

This high-dose quadrivalent vaccine presented higher efficacy in a randomized clinical trial versus a standard-dose influenza vaccine for preventing laboratory-confirmed influenza illness in adults aged 65 or more [3]. Systematic reviews and meta-analyses, which included randomized and observational studies, assessed the effectiveness of high-dose inactivated influenza vaccines versus standard-dose influenza vaccines against influenza-related outcomes in 65 or more years old individuals [6,7]. The results support the evidence on the effectiveness of high-dose inactivated influenza vaccines compared to standard-dose influenza vaccines in preventing severe influenza outcomes in 65 or more years old individuals, with additional support from observational data [7]. Regarding severity-related outcomes, the high-dose quadrivalent influenza vaccine was more effective than the standard-dose influenza vaccine in preventing influenza-related hospitalisations, with a relative influenza vaccine effectiveness (rIVE) of 11.2% (7.4%-14.8%) for all seasons. Despite the important evidence of the effectiveness of the influenza vaccine (IVE) of the high-dose inactivated influenza vaccines for individuals aged 65 or older, only three studies in nursing homes were included [6]. Review studies indicated a need for further real-world population-based studies of high-dose influenza vaccines. Hence, it remains necessary to assess the clinical effectiveness of this vaccine in older adults living in LTCF [7–9].

In Portugal,in 2022–2023 season [10], the high-dose quadrivalent influenza vaccine began to be available exclusively and free of charge for individuals aged 65 or more living in long-term care facilities (LTCF). In the 2023–2024 season, access was expanded to community-dwelling individuals aged 65 or more, who could receive the vaccine in community pharmacies with co-payment upon medical prescription [11]. Since the 2024–2025 season the high-dose influenza vaccine is available for individuals aged 60 or more and offered free of charge to all individuals aged 85 or more, regardless of residence setting, in addition to continued free access for residents in LTCFs and similar institutions [12].

Given the scarcity of reported high-dose IVE estimates for this population and the Portuguese strategy of vaccinating institutionalised individuals aged 65 or more, it is crucial to evaluate the vaccines effect on preventing severe outcomes in this age group of the Portuguese population. Thus, the objective of this study is to estimate the rIVE of the high-dose quadrivalent influenza vaccine against hospital admission due to influenza-like-illness in individuals vaccinated with any influenza vaccine and the absolute IVE of the high-dose quadrivalent influenza vaccine against hospital admission due to influenza-like-illness in individuals eligible for the high-dose quadrivalent vaccine, using data routinely collected in electronic health records (EHR) in mainland Portugal.

## Methods

### Study design and population

A retrospective cohort study using data collected routinely in EHR databases will be implemented. For the estimation of rIVE, only vaccinated individuals will be included, either with the high-dose or the standard influenza vaccine. For the estimation of absolute IVE, individuals eligible for the high-dose influenza vaccine during the study period will be included. For both cohorts, we will consider two subgroups: community-dwelling individuals aged ≥85 years and individuals living in LTCF. The cohorts are represented in Fig 1, with panel A representing rIVE and panel B absolute IVE.

**Fig 1 pone.0314177.g001:**
[figure not shown]
Diagram of the two cohorts designed in this study. A – cohort of vaccinated individuals to measure relative influenza vaccine effectiveness, B – cohort of individuals eligible for the high-dose influenza vaccine to measure absolute influenza vaccine effectiveness. For the two cohorts, we will consider two subgroups: community-dwelling individuals aged ≥85 years and individuals living in LTCF and each cohort will begin every influenza season.

We will use a fixed cohort approach, defining the eligible population by their age at the start of the vaccination campaign(s) and living status. Table 1 describes the connection between the cohorts and the objectives.

**Table 1 pone.0314177.t001:** Summary of the study design with the different cohorts, objectives and exposed and unexposed groups.

Cohort	Subgroup	Objective	Exposed	Reference group
Vaccinated individuals (Fig 1, panel A)	Individuals living in LTCF	Estimate relative IVE of the high-dose quadrivalent influenza vaccine	Vaccinated with high-dose quadrivalent influenza vaccine	Vaccinated with standard influenza vaccine
	Individuals living in the community (≥85 years)			
Individuals eligible for influenza vaccination (Fig 1, panel B)	Individuals living in LTCF	Estimate absolute IVE of the high-dose quadrivalent influenza vaccine	Vaccinated with high-dose quadrivalent influenza vaccine	Unvaccinated individuals eligible for the high-dose quadrivalent influenza vaccine
	Individuals living in the community (≥85 years)			

IVE – influenza vaccine effectiveness; LTCF – long-term care facilities

### Inclusion and exclusion criteria

The study population includes all registered individuals without contraindications for influenza vaccination residents in mainland Portugal. Only vaccinated individuals with the high-dose quadrivalent or standard influenza vaccine living in LTCF or community-dwelling individuals aged 85 or older will be included to estimate rIVE. Whereas, to estimate absolute IVE, only eligible individuals for the high-dose influenza vaccine living in LTCF or community-dwelling individuals aged 85 or older will be included.

We will exclude individuals with inconsistent or missing data on vaccination (e.g., any vaccination date unknown and any vaccine brand unknown), individuals who received any vaccine brand not approved by the European Medicines Agency (EMA), and individuals vaccinated before the study started.

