### Study setting and period

To estimate rIVE, the study population will include individuals vaccinated with the high-dose or standard influenza vaccine in mainland Portugal between the 2022/2023 and 2024/2025 seasons. When applicable, we will analyse each season (2022/2023, 2023/2024, 2024/2025) individually, starting after the implementation of each influenza vaccination campaign and ending nine months thereafter.

To estimate absolute IVE, the study population will include individuals for whom the high-dose influenza vaccine has been recommended in mainland Portugal for the 2024/2025 season. The study period will start after the implementation of the influenza vaccination campaign period and end nine months thereafter.

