### Vaccination status

To estimate rIVE, the vaccination status will be assessed retrospectively, and the time since vaccination will be estimated. The exposure of interest will be to receive the high-dose quadrivalent influenza vaccine, and the comparison group will be composed of those who received the standard-dose influenza vaccine.

To estimate absolute IVE, the vaccination status will be assessed as a time-changing variable according to the following classification:

◦ Unvaccinated: person-time of individuals without any quadrivalent influenza vaccine in the season.◦ Vaccinated: person-time of individuals who received a high-dose quadrivalent influenza vaccine dose during the study period. The completion status is achieved 14 days after administration of the dose.

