#### Time-changing characteristics (to estimate absolute IVE).

Vaccination status and time since vaccination will be assessed, and individuals will be classified into the same or updated vaccination status daily, generating a new record in the dataset for each new assessment. Person-time exposure between 0 and 13 days after vaccination will be excluded from the analysis.

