#### Censoring events.

All individuals will be followed from the start of the vaccination campaign until:

◦ Hospitalisation date (corresponding to the event date);◦ At the end of the study (nine months after the start of the vaccination campaign);◦ On the date of death (any cause)

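### Absolute-IVE cohort: excluding whole people for a faulty dose recorded after follow-up starts deletes valid unvaccinated time and can bias absolute IVE slightly upward

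*Protocol article*

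**What the plan says.** Protocol article, Inclusion and exclusion criteria: "We will exclude individuals with inconsistent or missing data on vaccination (e.g., any vaccination date unknown and any vaccine brand unknown". The same sentence removes anyone given a brand without EMA approval "and individuals vaccinated before the study started". The unit removed is the person, and no separate rule is given for the absolute-IVE cohort.

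For that cohort, three other sections fix the time structure:

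- Censoring events: "All individuals will be followed from the start of the vaccination campaign until" admission, death or the nine-month end of study. A faulty dose is not among the censoring events.
- Vaccination status: "To estimate absolute IVE, the vaccination status will be assessed as a time-changing variable".
- Time-changing characteristics: "individuals will be classified into the same or updated vaccination status daily". The same section drops the person-time of days 0 to 13 after a dose but keeps the person.

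Description of the sample selection says that the number and proportion removed by each criterion will be recorded.

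**The concern.** People already vaccinated at study start are excluded, so in anyone otherwise retained a season dose, and any fault in its record, falls after time zero. Before that dose the person contributes correctly classified unvaccinated time. The exclusion removes this time because of something that happens later.

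The removal is one-sided. A never-vaccinated person has no season dose record that can fail. A person who dies in an admission before any dose cannot later acquire a faulty record, so that event stays in the reference group. A person who stays well and later receives a badly recorded dose is removed with all earlier unvaccinated time. Where this asymmetry operates, the unvaccinated hazard is too high and absolute IVE is too high. An avoidable bias in favour of the vaccine is unwelcome in an estimate meant to inform the national programme.

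**Working it through.** The article gives no fault rate, expected coverage or event count, so it has no figure to reproduce. The check asks for direction and size under stated assumptions.

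**Inputs from the article.** Person-level exclusion; follow-up from campaign start; daily-updated exposure; days 0-13 after a dose dropped; Cox regression with IVE = (1 - aHR) x 100; 272 days, the end of the last time-since-vaccination class, used as the length of follow-up.

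**Assumptions.** Share f of vaccinees with a faulty season record: 1% to 20%. Coverage c: 60% or 80%. Vaccination day: mean 30 (SD 15) or mean 45 (SD 25). Events: peak at day 110, peak at day 60, or flat. True IVE: 40% or 10%. Faults unrelated to risk.

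**Step 1: direction.** Let the unvaccinated group have E events in person-time T, and let q be the share of T that comes from people vaccinated later.

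- If an event prevents any later dose, no one with an unvaccinated event is ever removed. E stays and T becomes T(1 - fq). The reference rate rises by 1/(1 - fq), so the HR is multiplied by (1 - fq).
- Vaccinated events and time both shrink by (1 - f), so the vaccinated rate is unchanged.
- If an event does not change later vaccination, events are removed in the same proportion as time. The factor cancels and the bias is zero.

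**Step 2: crude size.** Ignoring deaths, with mean dose day d, q = cd / [cd + (1 - c) x 272].

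- c = 60%, d = 30: 18 / (18 + 108.8) = 0.14
- c = 80%, d = 30: 24 / (24 + 54.4) = 0.31
- c = 80%, d = 45: 36 / (36 + 54.4) = 0.40

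With q = 0.40 and true IVE 40%, the reported IVE is 1 - 0.60 x (1 - 0.40f). This gives 1 - 0.60 x 0.992 = 40.5% at f = 2% and 1 - 0.60 x 0.96 = 42.4% at f = 10%.

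**Step 3: Cox scale.** The Cox model compares people on the same day, so only pre-dose time on days when events occur matters. The large-population Cox score equation was solved with events preventing any later dose. Results for true IVE 40% and coverage 80%:

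| Event pattern | Mean dose day | f = 2% | f = 5% | f = 10% |
|---|---|---|---|---|
| Peak day 110 | 30 | 40.01 | 40.02 | 40.04 |
| Peak day 110 | 45 | 40.10 | 40.25 | 40.51 |
| Flat | 30 | 40.06 | 40.15 | 40.31 |
| Flat | 45 | 40.14 | 40.35 | 40.70 |
| Peak day 60 | 30 | 40.19 | 40.47 | 40.93 |
| Peak day 60 | 45 | 40.53 | 41.32 | 42.64 |

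Every 60%-coverage result is smaller; the lowest are 40.00, 40.01 and 40.01. For true IVE 10% the ranges over all scenarios are 10.00-10.82, 10.01-12.04 and 10.02-14.08. The extreme case, f = 20% in the last row, gives 45.27%.

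**Step 4: the condition, and the fix.** At f = 10%, if events leave later vaccination unchanged, every scenario returns 40.00% or 10.00%. If events halve later vaccination, the largest value for true IVE 40% falls from 42.64% to 41.35%. Removing no one on later information returns the true IVE exactly. For dated doses this is equivalent to keeping the person and censoring at the dose.

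**The case against.** **The bias is not automatic.** A reader might infer that the rule always deletes event-free time and so always inflates absolute IVE. The article does not support that. The exclusion is not limited to doses given before an event, so a person admitted first and given a badly recorded dose later is removed together with the event. This stands, and it makes the bias conditional.

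**The effect is small.** A reader might also reach for a larger figure: the crude formula with f = 10% and q = 0.7 gives 1 - 0.60 x 0.93 = 44.2%. But q = 0.7 at 80% coverage needs a mean dose day of about 159, and the Discussion anticipates possibly low coverage, which lowers q further. Registration is mandatory (Data sources), which gives no support for high fault rates, and the exclusion counts will show f. All of this stands for size. Counting exclusions reveals the problem but does not correct it.

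**The texts are compatible.** One section defines who is analysed and the others define how exposure is coded, so both can be applied together. That is right: this is not a formal contradiction but a person-level rule that fits a time-changing exposure badly.

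**Other readings exist.** The vaccination data at issue could include records from before time zero. Study setting and period says "The study period will start after the implementation of the influenza vaccination campaign period and end nine months thereafter", which leaves time zero less clear than Censoring events does. The definition "Unvaccinated: person-time of individuals without any quadrivalent influenza vaccine in the season" could be read at person level, in which case pre-dose time would not count at all. Daily updating argues against that last reading. Under the others, the point still applies to any faulty dose given after follow-up starts.

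**This is detail for a fuller document.** A missing censoring rule alone might be. But the person-level exclusion is stated, and it is that stated rule which does the damage.

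**Conclusion.** The point holds in a limited form. In the absolute-IVE cohort, the exclusion conditions membership on information arising after time zero and discards valid unvaccinated time from future vaccinees only. Any resulting bias favours the vaccine, and it arises only as far as admission or death lowers the chance of a later dose. Some asymmetry is likely, since a fatal admission rules out a later dose, but the article gives nothing to quantify it.

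With events preventing all later doses, the bias for a true IVE of 40% is about 0 to 0.5 points at a 2% fault rate and 0 to 2.6 points at 10%. It is at most 0.04 points at 10% when the mean dose day is 30 and the peak is at day 110. The top of the range needs late vaccination, an early epidemic and 80% coverage together. These figures rest on assumed fault rates, coverage and timing, and on faults being unrelated to risk. Minor priority, but cheap to remove.

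**What to change.** In Inclusion and exclusion criteria, limit whole-person exclusion for faulty vaccination data or an unapproved brand to:

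- faults known at campaign start;
- the rIVE cohort, where a valid dose defines entry;
- in the main absolute-IVE analysis, season doses without a reliable date.

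In Censoring events, add for absolute IVE: a person whose season dose has a reliable date but an unknown brand, an otherwise inconsistent record or an unapproved brand counts as unvaccinated until that date and is censored there. This parallels the handling of days 0-13, where person-time is dropped and the person kept.

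For undated doses, add a sensitivity analysis that retains these people as unvaccinated up to the earliest, and then the latest, possible dose date. Censoring undated doses at campaign start would not help: it leaves no follow-up and is the same as exclusion.

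The cost is one revised sentence, one added censoring event, one sensitivity analysis and slightly more programming. No new data are needed, and the article says that data access had not yet been obtained at submission.

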### Study setting and period

To estimate rIVE, the study population will include individuals vaccinated with the high-dose or standard influenza vaccine in mainland Portugal between the 2022/2023 and 2024/2025 seasons. When applicable, we will analyse each season (2022/2023, 2023/2024, 2024/2025) individually, starting after the implementation of each influenza vaccination campaign and ending nine months thereafter.

To estimate absolute IVE, the study population will include individuals for whom the high-dose influenza vaccine has been recommended in mainland Portugal for the 2024/2025 season. The study period will start after the implementation of the influenza vaccination campaign period and end nine months thereafter.

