### Stratification variables

If possible, and when applicable, rIVE will be estimated for each seasonal campaign.

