### Estimation of the vaccine effectiveness

A complete case analysis will be performed considering all variables in the final model to estimate adjusted-confounding IVE and stratified for each subgroup, individuals linving in LTCF and individuals living in the community (≥85 years)

We will use Cox proportional hazards regression models to estimate the hazard ratio (HR), considering the event the first hospitalisation due to influenza-like-illness and as exposure the vaccination status. The crude HR of vaccinated with the high-dose influenza vaccine vs vaccinated with the standard dose (rIVE) or unvaccinated (absolute IVE) will be estimated for each outcome of interest during the study period, without adjusting for other factors or covariates.

We will consider two sets of confounding factors. First, we will estimate partially adjusted HR, adjusting by age, sex and country region. Age will be modelled using a restricted cubic spline, with knots specified according to Harrell [12]. Second, a fully adjusted HR estimate will be produced by adjusting variables related to socioeconomic condition, comorbidities and health-seeking behaviour. IVE will be estimated as one minus the confounder-adjusted HR of vaccinated vs vaccinated with the standard dose (rIVE) or unvaccinated (absolute IVE) for each outcome of interest.

IVE = (1 - aHR) * 100

To estimate relative IVE, the time since vaccination will be modelled using a restricted cubic spline, with knots specified at zero and 15 days and then at the 40^th^ and 90^th^ percentile. To estimate absolute IVE for the time since vaccination (secondary objective), IVE will be estimated by comparing the hazard rate of the outcome in individuals vaccinated with the high-dose influenza vaccine for each class of the time since vaccination - 14–89 days, 90–179 days and 180–272 days (exposed group), in comparison with the outcome hazard rate in unvaccinated individuals (reference group).

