#### Propensity score matching.

Individual characteristics might influence vaccination status, leading to systematic differences between those vaccinated with different vaccines and those vaccinated (rIVE) and unvaccinated (absolute IVE). Propensity score matching is a statistical technique used to reduce selection bias in observational studies by creating a matched set of treated (vaccinated with high-dose influenza vaccine) and untreated (vaccinated – rIVE and unvaccinated – absolute IVE) individuals with similar propensity scores. The first option will be matching without replacement, 1-to-1. However, considering the vaccination coverage, this ratio might need to be reviewed.

Several assumptions should be met to ensure that conditioning on the propensity score will lead to unbiased estimates of average treatment effects. The first one is that there should not be unmeasured confounders, i.e., the variables affecting vaccination status and hospitalisation due to influenza-like-illness should have been measured. The second relates to positivity, each individual should have a non-zero probability of getting the high-dose influenza vaccine. Additionally, the propensity score model should be correctly defined, and there should not be any interference between individuals, i.e., an individual vaccinated with the high-dose influenza vaccine will not affect the hospitalisation of another individual. This final assumption has implications in estimating absolute IVE studies due to herd immunity since vaccinated individuals could indirectly protect unvaccinated individuals, leading to IVE underestimation. To account for potential violations of this assumption, we will consider statistical methods that account for clustering, which could be the geographical region of residence.

The propensity score will be estimated using logistic regression, where the vaccination status will be the outcome, and the baseline individual characteristics will be used to adjust. Then, the vaccinated with high-dose influenza vaccine and vaccinated (rIVE) or unvaccinated (absolute IVE) individuals with similar propensity scores will be matched, using nearest neighbour matching, and compared to ensure the balance of covariates. Once the balanced dataset is obtained, the Cox proportional hazards regression model will be used, with the adjustments mentioned in the section above to adjust for residual confounding [13].

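### The relative-IVE cohort is not limited to people with access to the high-dose vaccine, and nothing keeps product from being confounded with season in a combined community estimate

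*Protocol article*

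**What the plan says.** All references are to the protocol article.

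- **Access to high dose.** Background states that in 2022/23 the high-dose vaccine "began to be available exclusively and free of charge for individuals aged 65 or more living in long-term care facilities". Community access followed in 2023/24, from age 65, through pharmacies on prescription and with co-payment. In 2024/25 it was available from age 60, free from age 85 in any setting, and still free for LTCF residents.
- **Who enters the rIVE cohort.** Study setting and period: "the study population will include individuals vaccinated with the high-dose or standard influenza vaccine in mainland Portugal between the 2022/2023 and 2024/2025 seasons". Inclusion and exclusion criteria: "Only vaccinated individuals with the high-dose quadrivalent or standard influenza vaccine living in LTCF or community-dwelling individuals aged 85 or older". Eligibility for high dose is a condition only for the absolute-IVE cohort, which is also confined to 2024/25.
- **Positivity.** The propensity score section requires that "each individual should have a non-zero probability of getting the high-dose influenza vaccine".
- **Season.** Study setting and period: "When applicable, we will analyse each season (2022/2023, 2023/2024, 2024/2025) individually". Stratification variables: "If possible, and when applicable, rIVE will be estimated for each seasonal campaign". The Fig 1 legend adds that "each cohort will begin every influenza season".
- **Adjustment.** Estimation of the vaccine effectiveness: "First, we will estimate partially adjusted HR, adjusting by age, sex and country region". The full model adds socioeconomic condition, comorbidities and health-seeking behaviour. The propensity model uses baseline individual characteristics. Season and calendar time are named in none of these places.

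**The concern.** By the protocol's own account, a community resident aged 85 or older vaccinated in 2022/23 could receive only the standard dose. Such people meet the rIVE inclusion rule and can stand only in the reference group. In 2023/24 access existed but was restricted, so high-dose use in the community was probably low until 2024/25.

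If seasons are combined, most high-dose follow-up comes from 2024/25 and most standard-dose follow-up from earlier seasons. Follow-up runs from each campaign's start, so an unstratified Cox model places people from different epidemics in the same risk set. Matching on personal characteristics does not prevent this: a 2024/25 high-dose recipient can be paired with a similar 2022/23 standard-dose recipient, and balance checks on the listed covariates would look satisfactory. The hazard ratio would then partly measure the difference between influenza seasons. The results are meant to inform national vaccine policy, and the effect cited in Background is small (11.2%), so a modest season difference could hide it, inflate it or reverse its sign.

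**Working it through.** The article gives no sample size, event count, high-dose share or season incidence, so there is no planned figure to reproduce. The check sets the sections side by side and then illustrates the size of the bias.

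**Step 1: access against entry, community aged 85 or older**

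| Season | High-dose access (Background) | Admitted to rIVE cohort | High-dose arm possible |
|---|---|---|---|
| 2022/23 | none | yes | no |
| 2023/24 | prescription and co-payment | yes | yes, restricted |
| 2024/25 | free | yes | yes |

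The first row conflicts with the positivity condition.

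**Step 2: bias in a combined estimate without season**

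Inputs:
- True HR = 1 - 0.112 = 0.888. The 11.2% is from Background and serves only as a scale.
- High-dose share p in the three seasons: 0, 0.05, 0.80. The 0 follows from Background; the other two are assumed.
- Season hazard r: 1, 1 and k, with k from 0.67 to 1.5 (assumed).
- Three seasons of equal size (assumed).

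Formula: combined HR = [Σ(p·r·0.888) / Σp] ÷ [Σ((1-p)·r) / Σ(1-p)].

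For k = 1.5:
- High dose: (0 + 0.05 + 0.80×1.5)/0.85 = 1.4706; ×0.888 = 1.3059.
- Standard dose: (1 + 0.95 + 0.20×1.5)/2.15 = 1.0465.
- HR = 1.3059/1.0465 = 1.248, so rIVE = -24.8%.

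For k = 0.67:
- High dose: (0.05 + 0.536)/0.85 = 0.6894; ×0.888 = 0.6122.
- Standard dose: (1.95 + 0.134)/2.15 = 0.9693.
- HR = 0.6122/0.9693 = 0.632, so rIVE = +36.8%.

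Under these shares, 1.95/2.15 = 91% of standard-dose recipients come from the two earlier seasons, and 0.80/0.85 = 94% of high-dose recipients from 2024/25.

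| k | True 11.2%, shares 0/5/80% | True 11.2%, shares 0/5/50% | True 0%, shares 0/5/80% |
|---|---|---|---|
| 0.67 | 36.8% | 33.4% | 28.9% |
| 0.8 | 26.5% | 24.3% | 17.3% |
| 1 | 11.2% | 11.2% | 0% |
| 1.25 | -7.2% | -3.7% | -20.7% |
| 1.5 | -24.8% | -17.2% | -40.5% |

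These are crude rate ratios. The listed covariates are personal characteristics, so adjusting for them would not be expected to remove a difference in epidemic intensity.

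**Step 3: when the bias vanishes**

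If r is constant, both average hazards are equal and the HR is 0.888. If p is constant, both arms weight the seasons identically and the HR is again 0.888. Estimation within season, or a baseline hazard stratified by season, also removes the season bias by construction.

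**Step 4: LTCF**

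With assumed high-dose shares of 70%, 80% and 90% and a true rIVE of 11.2%, the same formula gives 17.7% (k = 0.67) to 2.7% (k = 1.5). The season problem is smaller there because the share moves less.

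**The case against.** The strongest reply is that the article nowhere describes a pooled rIVE model. Right after defining the population, it plans to analyse seasons individually; the Stratification section repeats this, and the Fig 1 legend starts a cohort every season. Within one season, product cannot be confounded with season, and the 2022/23 community stratum, having no high-dose arm, could be set aside as not applicable. This stands in part. A reader might infer that the plan pools the seasons; the text does not say so. But season-specific estimation is conditional in both places, with no criterion, and the analysis section stratifies only by setting. If season-specific estimation is judged infeasible, a combined estimate is the natural fallback, and nothing protects it.

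A second reply is that the confounder list is open and that an article may leave a season term to the analysis plan. That is fair for the term alone. It does not explain why the entry rule admits a group that Background says had no access, while the absolute-IVE rule excludes people who were not eligible.

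A reader might also infer a large bias in LTCF, because the rIVE inclusion rule gives no age limit there. The documents do not support that. Age is adjusted by a restricted cubic spline, the Background describes the strategy as covering institutionalised people aged 65 or more, the eligible population is defined by age and living status, and the 2024/25 clause on LTCF access gives no age. What remains is a possible lack of overlap at younger ages. Nor must a 2022/23 community high-dose record be a misclassified LTCF resident: the Discussion also names vaccine-status error as a limitation.

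**Conclusion.** The concern holds for the community subgroup. The rIVE entry rule conflicts with the access history in Background and with the plan's own positivity condition, and no safeguard against season is fixed for a combined estimate. In such an estimate, a 20 to 25% difference in season incidence is enough to outweigh an 11.2% effect: with shares of 0/5/80%, a true 11.2% becomes -7.2% at k = 1.25 and 26.5% at k = 0.8. The wider range of about -25% to +37% belongs to k = 1.5 and 0.67.

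These figures rest on assumed shares, incidences and equal season sizes. They apply only if seasons are combined without regard to season, and they are not a forecast of the study's result. A constant share is implausible in the community given the access changes; a constant incidence cannot be judged from the document. The LTCF age limit is a secondary wording and overlap issue.

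**What to change.** 1. In Inclusion and exclusion criteria and in Study setting and period, restrict community rIVE to seasons with community access to high dose: 2024/25 as the main analysis, 2023/24 reported separately because access was selective, and 2022/23 dropped.
2. In Estimation of the vaccine effectiveness, either make season-specific estimation unconditional or, for any combined estimate, match within season and stratify the Cox baseline hazard by season. State the same in the propensity score section.
3. Reconcile the LTCF inclusion rule, which has no age limit, with the Background statements about residents aged 65 or more, and limit LTCF rIVE to the age range in which both products were available in that season.

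The cost is wording plus a strata term, and Data sources says that no data had been accessed at submission. The downside is fewer standard-dose events. Those lost from the 2022/23 community stratum offer no within-season comparison of the two products.
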